1. BACKGROUND

As a profession that necessitates 24 hour access to care, nursing demands a commitment to shift work. Traditionally, shift work involves working shifts outside of the typical daytime hours (1). Typically, permanent night shift (between 11 PM and 7 AM) and rotational shifts (shifts that rotate or change according to a set schedule) are of highest concern in regards to their health effects on nurses (2). It has been shown that the body is exposed to continuous stress when trying to adapt to new working hours (3). The ability to function has been internationally recognized as one of many health implications of nurses on shift work (4).

- 1. FATIGUE
     1. CAUSES OF WORK-RELATED FATIGUE

Current evidence does not delineate a single source of fatigue in the workplace, however, it has been hypothesized that long work hours, long hours of physical or mental activity, insufficient break time between shifts, inadequate rest, excessive stress or a combination of these factors may be associated with fatigue.

Circadian rhythms have been found to be associated with changes in mental and physical performance (5,6). This is of particular importance for those involved in shift work since some physiological functions are optimally regulated according to circadian rhythms suggesting that the body may not be well-suited for shift work.

- - 1. EFFECT OF FATIGUE ON HEALTH OUTCOMES

It has been suggested that fatigue may contribute to medical errors thereby causing negative health outcomes (7). A recent study identified 205 clinical errors and adverse incidents (e.g., medication errors, patient falls) reported by 201 night shift nurses over a one year period (8). A study of hospital-based nurses compared errors in nurses who worked permanent shift compared to rotating shifts and reported twice the odds of reporting a medical error due to tiredness (9). Other studies of hospital-based nurses report similar findings – longer shift hours were found to be associated with increased errors (10).

Some of the reported effects of work-related fatigue that may contribute to such outcomes are: reduced decision-making ability, reduced attention and vigilance, reduced reaction time, increased errors in judgement, increased forgetfulness and increased absenteeism. A large health technology assessment report conducted for the Agency of Healthcare Research and Quality assessed the aspects of fatigue that concerned sleep and their effect on medical errors, states that although fatigue is common cited as a risk factor for medical errors, it may in fact be over-represented in situations that lead to error and must be further studied (11).

- - 1. PREVALENCE OF SHIFT WORK AND FATIGUE IN NURSING

Approximately 20% of the US workforce participates in shift work (12) including almost one-third of full-time nursing professionals (2). Nineteen to 29% of shift workers are thought to experience fatigue (13). Studies comparing shorter shifts (8 hr) to longer shifts (12 hr) found that while some workers preferred the benefits of the longer shift (i.e. shorter work week), fatigue and decreased alertness was experienced near the end of the shift (14). One large cohort study including female nurses found shift work, particularly night duty (*p*<0.001), to be the most important predictor of fatigue (15).

- - 1. DEFINING FATIGUE

Fatigue is a subjective and heterogeneous experience, making an exact definition difficult to capture. Since the proposed study intends to measure work-related fatigue, we will refer to fatigue as that outlined by the Canadian Centre for Occupational Health and Safety: the state of feeling very tired, weary or sleepy resulting from insufficient sleep, prolonged mental or physical work, or extended periods of stress or anxiety (16).

- - 1. TREATMENT OF FATIGUE

Work-related fatigue may be best-managed by better regulation of working hours, especially for those involved in shift work. In Canada and the US, nursing work hours are self-regulated and nurses are expected to use professional judgment to determine whether fatigue might interfere with their performance and, if so, to refrain from practising. Although there is general consensus that a reduction in working hours is necessary, there is little incentive to do so.

A variety of educational and administrative interventions have been employed to help health care personnel adapt to working shifts however, these are difficult to implement on an already strained health care system. There is currently no cure or specific medical treatment for fatigue. Treatment, if used, is aimed to reduce symptoms of fatigue such as loss of memory and concentration, headache, sleep problems and exhaustion. Such treatments may include: anti-anxiety medications, antidepressants, and dietary changes. However, some medications, such as antidepressants or stimulant medications may have unintentional consequences such as dependency (17).

Natural health products (NHPs)[[1]](#footnote-2), such as Echinacea for the common cold, are often explored for health maintenance and treatment of illness because of their perceived benefit and low risk of harm (18). However, there is a shortage of adequate, rigourous, clinical evidence on which to base therapeutic claims. Despite this, North Americans are increasingly using NHPs. In Canada, 70% of people were had used at least one NHPs in 1999 and 26% had used three or more; these number grew to 75% and 31%, respectively, by 2001 (19).

NHPs for stress and fatigue is becoming an increasingly popular topic of clinical study. For instance, a Cochrane systematic review examining Traditional Chinese Medicine for fatigue is currently being conducted (20). Another review of melatonin for sleep disorders, included an examination of the NHP for shift work in which five randomized controlled trials (RCTs) were identified (21,22). The review found that melatonin did not significantly reduce sleep problems (sleep onset latency and sleep efficiency) associated with shift work. Other NHPs have been studied according to their ability to help the body to adapt to different conditions of stress (23-25); one such NHP is *Rhodiola rosea*.

- 1. RHODIOLA ROSEA

*Rhodiola rosea* is a flowering biennial grown at high altitudes in northern latitudes and has been a part of traditional medicine systems in parts of Europe, Asia and Russia for centuries. Due to its adaptogenic properties, it has received attention from the scientific community. The term adaptogen refers to natural herbal products most commonly which are “non-toxic in normal doses, produce a non-specific response and have a normalizing physiologic influence” (26). Similarly, *R. rosea* has been referred to as an ergogenic aid - an herb used to enhance physical and mental performance. Common health indications in *R. rosea* literature pertain to its performance-enhancing and mental stress-reducing properties. Further claims of *R.rosea’s* stress alleviating properties along with immune enhancement and influence on sexuality have recently been showcased in the lay media (e.g. *The Oprah Winfrey Show*). The published literature suggests that these claims may not be well-substantiated.

- - 1. IS RHODIOLA ROSEA BENEFICIAL FOR TREATMENT OF FATIGUE?

A systematic review conducted by our research team identified 11 clinical trials examining the effect of R. rosea and on physical endurance and mental fatigue (Table 1) (27). Two of four RCTs examining *R. rosea* alone for physical performance indicate that the herb, standardized to 3% rosavins, may increase exercise endurance capacity (28,29). Two RCTs examining *R. rosea* in combination with other substances for this indication found that *R.rosea* had no significant effect on physical performance. Of five RCTs of *R. rosea* for enhancing mental performance identified, three indicated that the herb may be effective in improving overall health in a mentally fatigued population (30-32), however in two of these studies, fatigue measurement tools do not appear to be validated, raising concern about the overall validity of their findings. The two remaining studies of mental fatigue offer inconclusive or negative results. Research regarding *R.rosea* efficacy is contradictory. While some evidence suggests that the herb may be helpful for enhancing physical performance and alleviating mental fatigue, the literature reviewed has many methodological flaws and limits accurate assessment of *R. rosea’s* efficacy. A well-designed RCT is needed to determine the true efficacy of *R.rosea* for physical or mental fatigue*.*

- - 1. IS RHODIOLA ROSEA INDICATED FOR TEATMENT OF FATIGUE FOR NURSES ON SHIFT WORK?

Two trials were identified which examine *R. rosea* for fatigue in subjects participating in shift work. One study evaluated *R. rosea* for non-specific fatigue was evaluated in a double-blind crossover RCT in 56 physicians on night duty (33). Participants were randomized to either 170 mg *R. rosea* (standardized to 2.6% salidroside) or placebo. The study period lasted for two weeks followed by a two-week wash-out period, after which participants received the opposite intervention for two weeks. The primary outcome was fatigue, measured using a fatigue index which authors state was specifically developed for use in this study; the tool does not appear to be validated. It is comprised of a composite of scores on five tests that aim to measure speed of visual and auditory perception, attention capacity and short-term memory. Measurements were carried out before and after the treatment period. Authors indicate a significant improvement in the fatigue index after two weeks of *R. rosea* supplementation but provided no statistical evidence for this conclusion. In addition, the authors mention that physicians were on night duty for ‘considerably’ longer during the second period of crossover than the first, however do not state how much longer or provide rationale. As such, findings of this study must be interpreted as inconclusive. Further RCTs with a transparent analytical approach are needed.

Another RCT conducted in Russia evaluated the effect of two different single doses of *R. rosea* on mental fatigue in 121 male military cadets (19-21 years) (31). Subjects were randomized to take 370 mg or 555 mg of *R. rosea (s*tandardized to 2.4% salidroside)or placebo. A non-treatment group was also included, however subjects were not randomized into this group and comparisons against this group is not considered when drawing conclusions. The intervention was taken at 4:00am while participants were on an overnight shift (starting at 6:00pm). Capacity for mental work, measured using a fatigue index of unknown origins, and with no evidence of its psychometric properties, and pulse pressure and rate were evaluated before night duty and one hour after taking the study medication. A self-report questionnaire evaluating general well-being was completed after taking the study medication. The fatigue index was comprised of three parameters: visual perception, short-term memory and perception of order. Improvements in favour of both doses of *R. rosea* were apparent in the fatigue index (*p*<0.001); no significant differences between groups occurred for other outcomes. The method of randomization was unclear and similar to the previous study, the outcome measure does not appear to be validated.

The findings from the above studies are not without major methodological flaws – inappropriate outcome measurement tools and inappropriate analysis approach. The assessment of efficacy of *R.rosea* for fatigue-alleviation in shift-workers would benefit from a well-designed, rigourously conducted RCT.

- - 1. IS RHODIOLA SAFE FOR USE IN THIS POPULATION?

Out of 446 subjects examined in the 11 included clinical studies of physical and mental fatigue, five adverse events were mentioned in three studies. Two subjects on 200 mg of *R. rosea* over a 4-week period each experienced a minor and serious headache (34); one subject on placebo over a 2-day treatment period experienced a minor headache and another had insomnia (29). Another subject on placebo experienced hypersalivation (31). There appear to be few side effects associated with *R. rosea* supplementation; those identified are of a mild nature.

From the available literature, the largest dose of *R.rosea* taken for the longest period of time without side effects is 340 mg twice per day over a six week period. No other adverse effects from case studies or case reports have been identified and available clinical evidence suggests *R. rosea* has a safe profile with little toxicity. The lethal dose of *R. rosea*, at which 50% of animals die (LD50), has previously been found to be 3360mg/kg in rats (35). Equivalence calculations have indicated that in adult humans, LD50 would be approximately 235,000 mg/kg(36). Clinical studies in the literature report *R. rosea*-only products ranging in dose from 50 mg to 660mg *R. rosea* extract per capsule, to a maximum of 1500mg/day suggesting a large margin of safety. Further, *R. rosea* is available in Canada as a natural health product (i.e. for over-the-counter use as self-care, without a physician’s supervision). In the United States, it is marketed as a dietary supplement which are deemed safe based on a documented history of use or other evidence of safety unless proven otherwise (37). While neither Health Canada nor its US counter-part has issued any safety concerns about *R. rosea,* one product containing *R. rosea* was recalled by the Food and Drug Administration in December 2008 for adulteration with a drug product (hydroxyhomosildenafil – an analog of the active ingredient in a drug used for erectile dysfunction).

Although no contraindications with other herbal or prescription medications currently exist, we postulate that *R. rosea* may have an additive effect with other substances exhibiting stimulant properties and such combination is contraindicated (38). Like many natural health products, the likelihood of adequate reporting of adverse events may be lower than conventional medications due to the inconsistent nature in which patients encounter NHPs – non-standard doses, varying durations and combined with any number of other NHPs or conventional medicines (39).

No safety information currently exists for pediatric, breast-feeding and pregnant populations.

- - 1. RHODIOLA ROSEA FORMULATION TO BE USED

Of the many challenges to NHP research, product heterogeneity and standardization are of paramount concern when selecting a formulation for study. Unlike drug development where a drug is built around an active compound, NHP development works in the reverse order since, in nature, identification of the plant comes before isolation of the compounds it contains. In addition, the therapeutic effects of most NHPs are not typically attributable to a single, compound. Instead, a plethora of compounds, called active constituents, may be responsible for an NHP’s effect.

While it is currently unclear which specific compound(s) in *R. rosea* are active constituents, most preparations of *R.rosea* are standardized to specific levels of marker compounds rosavin, salidroside or both (40). Rosavin is the only constituent unique to the *R. rosea* from the Rhodiola genus; salidroside is common to most other Rhodiola species (41,42). The naturally occurring ratio of rosavins to salidrosides in *R. rosea* is approximately 3:1 and it has been recommended that *R. rosea* preparations reflect this ratio (43).

1. RATIONALE FOR PROPOSED STUDY

Most nurses working in hospital settings are involved in shift work. Although the consequences of this are numerous, many nurses prefer shift work as it allows them flexibility in terms of time and earnings. In addition, it should be noted that in Canada, there are no thresholds or limits to the number of hours worked by nursing professionals. Nursing work hours are self-regulated and development of policies and legislation around this is unlikely forthcoming. As such, some nurses may want an alternative to working fewer hours to help reduce their level of fatigue and/or sleepiness.

From the evidence presented herein, it is apparent that a safe and effective intervention to reduce fatigue in nurses on shift work does not currently exist. Although there have been at least 11 trials examining the effects of *R. rosea* on fatigue or related conditions, none are of adequate quality or methodology to warrant recommendation of use in the target population. Further RCTs of high methodological quality and adequate, evidence-based sample sizes are required to establish the true usefulness of *R. rosea* for fatigue.

1. OBJECTIVES

The primary objective of this trial is to assess whether Rhodiola rosea improves fatigue when compared to placebo in nurses involved in shift work. We will also carry out psychometric testing of the Adaptive Capacity Index.

1. Population

Patients meeting the following inclusion criteria and none of the exclusion criteria will be considered for enrolment in the study.

- 1. INCLUSION CRITERIA

1. Fourth year nursing students enrolled in NURS 495 (Nursing Practice) in the Winter 2011 term at the University of Alberta;
2. Participating in permanent overnight (between 11 P.M. and 7 A.M.) or rotating shift work (shifts that rotate or change according to a set schedule);
3. Otherwise healthy***~~*~~***~~;~~
4. Consent to participate in the study;

***Population justification:*** upon consultation with nurses, nurse managers and the University of Alberta’s Faculty of Nursing undergraduate coordinator, this is the most homogeneous population of nurses and offers a large recruitment base (n>200). Since there is no clear diagnosis criteria for fatigue, all nurses on shift work meeting inclusion criteria will be considered for inclusion.

- 1. EXCLUSION CRITERIA

1. Nurses aged 18 years or younger (safety data for this age group does not exist);
2. Breastfeeding or pregnant women, as confirmed by a blood test (safety data for these groups do not exist);
3. ***Female participants with child bearing potential not practicing a form of birth control throughout the trial;***
4. Presence of a primary medical condition associated with fatigue (e.g. cardiac, gastrointestinal, respiratory, renal, rheumatologic, or oncologic disease);
5. Presence of schizophrenia, bipolar disorder, dementia, eating disorders, insomnia or substance abuse;
6. Presence of diabetes*;*
7. Concurrent utilization of hypoglycaemic agents for raising or lowering blood pressure***;***
8. Known allergy or hypersensitivity to R. rosea or Sedum family extracts or pollen;
9. Known allergy to microcrystalline cellulose or silicon dioxide;
10. Concurrent utilization of stimulant drug such as methylphenidate (Ritalin) amphetamine (Dexedrine, Adderall) methamphetamine (Desoxyn) and pemoline (Cylert);
11. Concurrent utilization of other rhodiola or ginseng products (both fall in the same therapuetic category known as an "adaptogen").
12. Any significant medical condition
13. Any neurological or mental health condition
14. Taking medication that has central nervous system effects;
15. Aged 55 years or older;
16. Low blood pressure or history of significant dizziness
17. trial design

Participants will be randomized to receive either *R. rosea* or identical placebo to be taken daily over a six week period (Error: Reference source not found).

Randomize

Population

Eligible

Sample

Placebo

No intervention

*Rhodiola rosea*

Enrolment (4 weeks before trial start)

Baseline (start of clinical rotation)

Week 10

(End of clinical rotation)

Week 3

Week6

**Figure 1:** Trial Design Schematic

- - 1. RECRUITMENT, informed consent and enrollment

In collaboration with the Faculty of Nursing, students enrolled in NURS 495 will receive notification of the study by way of an introductory email with an information sheet attached in December 2010. The ~~study~~ **project** coordinator will make in-class visits during the first two weeks of January 2011 to answer any study-related questions and to schedule an appointment for eligibility assessment with the study nurse for interested persons. During the eligibility assessment subjects will be given the information sheet to read over and have study procedures explained to them in detail by the study nurse***.*** Subjects will sign the consent form prior to being screened against the selection criteria***.*** All eligible subjects will then be enrolled, randomized and receive their assigned medication from the study nurse during the first visit. However, female participants will need to undergo a blood pregnancy test to ensure they are not pregnant for which they will be given a lab requisition by the study nurse. A total of 2 mL of blood will be withdrawn for this test***.*** When lab results are received by the principal investigator, those with tests confirming they are not pregnant will contacted by the study nurse to confirm their enrolment. Females whose tests indicate positive for pregnancy will be called by the study physician ([name]) and asked to return the study medication they received to the study nurse. The participant will then be contacted by the study nurse to schedule a drop-off date and time. During the enrolment visit, the study nurse will also review all outcome measurement tools and walk subjects through a pilot of the tools to be used during the study.

All participants will begin the study on the same, fixed date when their shift work begins (date to be finalized in January 2011). Since data collection will be electronic via the internet, study participants are expected to have internet access. If participants know they will not have internet access or reliable access, arrangements will be made to give them either paper or offline electronic data collection forms (as well as a pre-paid envelope to send the forms back in).

- - 1. STUDY VISITS, phone calls and email reminders

In addition to the initial study visit and phone calls described in section 5.1.1., the project coordinatorwill phone each subject within 3 days of the study start to review study procedures and outcome assessment documentation procedures. At this time, the project coordinator will inquire about effectiveness of the blind and about participant beliefs about medication effectiveness. The next call from the project coordinator to participants will occur during the 2nd week of the study (days 14 to 20) inquire about adverse effects and to remind them of completion of the outcome assessment forms to be filled out~~.~~ The project coordinator will call study participants during the 5th week of the study (days 35 to 41) to remind them of the forms to be filled out, inquire about adverse effects and schedule a follow-up visit for when they are finished their clinical rotation at the end of 10 weeks. Throughout the study, subjects will also receive daily email reminders containing a link to the online data collection forms for that day. At the 10-week mark (day 70), participants will be sent an email reminder to complete all outcomes assessment forms for the final time. At this time, they will again be queried about their thoughts on effectiveness of the study medication. They will then return any unused study medication to the study nurse during their final scheduled visit.

1. trial INTERVENTIONS

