**The following interventions will be supplied:**

1. ***Rhodiola rosea* extract standardized to2.8% rosavins (**29.0 % microcrystalline cellulose, 0.5% Silicon dioxide
2. **Placebo (**95% microcrystalline cellulose, 0.5% Silicon dioxide)

**Both interventions will be encapsulated in gelatine capsules, which are an animal-based product, and will look identical. Medications will be packaged in identical bottles labelled according to the participants’ randomization code.**

Development of the both interventions will be undertaken by [name] [name], a pharmacist and assistant professor in the Faculty of Pharmacy and Pharmaceutical Sciences at the University of Alberta. [name], will store all trial medications (*R. rosea* and placebo) in a secured storage facility until recruitment. Study medication will then be given to the study nurse for dispensing at time of enrolment; medication will be stored under lock and key accessible only by the study nurse until time of dispensing.

- 1. Treatment regimen

The trial will begin on the day that subjects start their clinical rotations and end 6 weeks later. Subjects will be instructed to take two to four capsules of the trial medication per 24 hour period (see section 6.2). All outcomes will be measured at baseline (Day 0) and at the end of the trial period (week 6). The project coordinator will phone participants on the day(s) leading up to their baseline assessment to remind them to complete their questionnaires and ensure they are comfortable with the study procedures. The primary outcome and two secondary outcomes will be measured again at the end of each week; all other outcomes will be measured daily (see section 7). Subjects will be prompted to report adverse events daily during the trial period and at the end of their clinical rotation four weeks after completion of the trial. During the trial period, the study nurse will phone participants in week 2 and week 5to remind them to complete their questionnaires and to inquire about adverse events (see section 7.1.2).

- 1. DOSE AND DURATION

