**The code for a patient will only be opened in an emergency, when it is necessary for a patient’s treatment to be disclosed. If a code is broken the investigator will inform the Study Director/Monitor and document the details of the reason in the patient’s case report forms.**

- 1. ALLOCATION CONCEALMENT

Participants will receive a sealed, serially-numbered opaque bottle containing the study medication or placebo depending on their randomised group assignment. They will be provided a six-week supply of their assigned study medication.

- 1. BLINDING

**The placebo capsule will have the same appearance, volume, weight, odour and taste as the *R.rosea* product so that neither the participant nor trial personnel know who is receiving which medication. The effectiveness of the blind will be assessed at the beginning of the study after a single dose via the MYMOP on Day 1. Participants will be asked to guess which medication they think they were allocated to.**

- 1. **CO-INTERVENTION AND CONTAMINATION**

**Since stimulant medications have been identified as potentially hazardous to combine with *R.rosea*, subjects being recruited will be considered ineligible for the trial if they are using such medication. As part of their daily questionnaires, participants will be asked to record any medication used (prescription, over-the-counter, or natural health product) and quantity of caffeine and alcohol consumption in the past 24 hours to ensure that important co-variables can be considered in the final analysis. These questions will be administered as part of the daily MYMOP assessment.**

**From the start of the treatment, participants will be advised not to take any rhodiolaor ginseng preparations for the duration of the trial so that only the *R. rosea* treatment will influence trial outcomes. Furthermore, they will be informed that there is a 50% that they may be receiving *R.rosea*, the dose of which is being in this trial is the highest that has been supported by evidence of safety, and cautioned that they would therefore not want to “double-dose” themselves.**

- 1. **ACCOUNTABILITY OF TRIAL MEDICATION**

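### The allergy exclusions do not name gelatine, although both products are supplied in gelatine capsules

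*Protocol*

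**What the plan says.** Two items in the Protocol, section 4.2 (Exclusion criteria), deal with allergy to the trial products. Criterion 8 is "Known allergy or hypersensitivity to R. rosea or Sedum family extracts or pollen". Criterion 9 is "Known allergy to microcrystalline cellulose or silicon dioxide". The only other items that might reach an allergy are general: criterion 12, "Any significant medical condition", and inclusion item 3 in section 4.1, which asks that participants be healthy in other respects.

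The Protocol, section 6 (Trial interventions), gives the make-up of the two products. For the active product the listed excipients are "29.0 % microcrystalline cellulose, 0.5% Silicon dioxide". For the placebo the list is "95% microcrystalline cellulose, 0.5% Silicon dioxide". On the shell it says "Both interventions will be encapsulated in gelatine capsules, which are an animal-based product, and will look identical".

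**The concern.** The protocol did not rely on a general allergy clause. It named the components one by one, down to an excipient that makes up 0.5% of each product. With a list that specific, a screener may well take it as complete. The shell is the one stated component of both capsules that the list leaves out, and section 6 itself draws attention to its animal origin.

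What is at stake is the safety of an individual with a known gelatine allergy. Section 5.1.1 has eligible subjects enrolled, randomised and given their medication at the first visit. The only eligibility check described after dispensing is the pregnancy test. Section 7.1.3 withdraws anyone who comes to meet an exclusion criterion during the trial, but gelatine allergy is not one of those criteria, so that rule adds no protection.

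A smaller matter arises in the same part of section 6: the named placebo ingredients do not add up to the whole.

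**Working it through.** **Step 1. Each stated component against the criteria.** Components are from section 6, criteria from sections 4.1 and 4.2.

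| Component | Active | Placebo | Criterion that names it |
| --- | --- | --- | --- |
| *R. rosea* extract | yes | not listed | 8 |
| Microcrystalline cellulose | 29.0% | 95% | 9 |
| Silicon dioxide | 0.5% | 0.5% | 9 |
| Gelatine shell | yes | yes | none |

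Four components are stated. Three are named in the allergy criteria and one is not.

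**Step 2. Exposure to the unlisted component.** Section 6.2 asks for two capsules at the start of each wakeful period, with a further dose at the participant's discretion. Treatment lasts six weeks, to day 42. At full adherence and with no optional doses, that is 2 × 42 = 84 shells per participant, in either arm.

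**Step 3. Sum of the stated compositions.** The protocol gives no total, so there is no figure of its own to reproduce.

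- Active: 29.0 + 0.5 = 29.5%. The remainder, 100 − 29.5 = 70.5%, can be read as the extract.
- Placebo: 95 + 0.5 = 95.5%. The remainder, 100 − 95.5 = 4.5%, is not named anywhere in the text shown.

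For scale only: section 6.2 gives 182.0 mg of product per active capsule. Assume that the placebo contents weigh the same as the active contents.

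- If 182.0 mg is the whole contents, the unnamed part is 0.045 × 182 = 8.2 mg per capsule.
- If 182.0 mg is the extract alone, the contents weigh 182 / 0.705 = 258.2 mg and the unnamed part is 0.045 × 258.2 = 11.6 mg.

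The conclusion does not depend on either figure.

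**Step 4. Link to the statistics.** Gelatine allergy enters neither the sample-size calculation in section 8.1 nor the test of the vitality subscale in section 8.2. No power or error-rate calculation applies.

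**The case against.** The best defence is that the list is not silent. Criterion 12 and the inclusion item on being otherwise healthy give a screener grounds to turn away someone with a serious known allergy. This stands in part. It rules out saying that such a person would certainly pass screening. It does not close the gap, because neither item mentions allergy, and the protocol treats allergies separately in criteria 8 and 9.

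A reader might go further than the documents allow in three ways.

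- **Drop-out from refusing gelatine.** One might infer that people who avoid animal products would be randomised and then decline the capsules. Section 5.1.1 places the information sheet, the explanation of procedures and the signing of consent before screening. Someone who objects can decline at that point. The consent pages are not available, so it cannot be assumed that they fail to mention gelatine. The documents give no frequency for such refusal.
- **Bias in the adverse-event comparison.** Section 8.2 compares adverse-event rates between arms with a chi-squared test. Gelatine is in both arms, so randomisation should balance reactions to it. They would not be expected to bias the contrast.
- **A placebo that is not inert.** The unnamed 4.5% might suggest an active ingredient. Section 6.5 says "The placebo capsule will have the same appearance, volume, weight, odour and taste as the" active product, so a matching agent is one possibility. Others are plant material already covered by criterion 8, or a slip in a figure. Section 6 does not say whether its list is exhaustive, or whether the percentages refer to the contents or to the whole capsule. The bracket for the active product is not closed, so the text may be damaged here. No allergen and no activity is shown.

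**Conclusion.** The point holds as a minor safety gap. Criterion 9 and section 6 do not match: a known allergy to gelatine, present in every capsule of both arms, is not explicitly excluded and would be caught only through a general item at the screener's discretion. This rests on reading criteria 8 and 9 as the protocol's allergy screen, which is how they are written.

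Exposure is universal, but the number of susceptible candidates is probably very small and the documents give no figure for it. Sample size, error rates and the between-arm comparison are not affected. The 4.5% of the placebo that is not named is a missing formulation detail and supports nothing stronger.

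**What to change.** Reconcile exclusion criterion 9 with section 6, so that the allergy screen covers every stated component of both capsules, the shell included. Secondly, account for the placebo composition to 100% and state whether the percentages refer to the contents or to the whole capsule.

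This needs about one line in section 4.2 and one in section 6. The loss of eligible students should be negligible, and no part of the analysis has to change.
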